### Participant timeline

Eligible participants will complete the preoperative assessment (T1) one week prior to surgery, aligned with their routine preoperative medical consultation. Following THA and standard postoperative rehabilitation (about 3 weeks), participants who remain eligible will undergo the postoperative assessment (T2) at 6 + 2 weeks after THA. After T2, participants will be randomized to the two IGs or the CG. Following randomization, a one-time home visit (approximately 60 min) will be conducted, during which all participants will receive a tablet device with an introduction to its use, and study-arm specific instructions will be provided. During the 12-week intervention period, participants in the IGs will receive their respective intervention components, whereas the CG will receive usual care. Six months (± 2 weeks) after THA, the final assessment (T3) will take place. All assessments will be conducted on site at the Orthopaedic Clinic Heidelberg and will last approximately 1–1.5 h each. A schematic overview of participant flow, enrollment, intervention, and assessment time points is provided in the study flowchart (Fig. 1) and the participant timeline (Supplementary file 1).

### Interventions

#### Digital home-based exercise program: keep on keep up

Keep On Keep Up (KOKU) is a tablet-based, progressively structured strength and balance exercise program specifically designed for older adults at risk of falls [38]. It comprises 26 different strength and balance exercises based on the Otago Exercise Program [39], and the Fitness and Mobility Exercise (FaME) Program [40], which have been shown to improve physical capacity, reduce falls, and increase self-reported PA in older adults [41, 42]. Each exercise is accompanied by predefined goals and safety instructions displayed on the tablet and is demonstrated by an interactive virtual trainer avatar with audio guidance.

Participants allocated to the IGs will receive instructions in the use of the KOKU app during the home visit. Participants will be encouraged to use KOKU three times per week for approximately 15 min per session over the 12-week intervention period. After the intervention period, participants in the intervention groups may continue using KOKU indefinitely.

Each training session consists of three exercises. Progression to more challenging exercises occurs after a minimum of two weeks and is based on user feedback on perceived physical exertion and safety following each session. If both are rated as adequate, participants advance automatically to the next difficulty level (up to six levels), which is maintained for another minimum of two weeks.

After each exercise, participants are prompted to record the number of repetitions performed. The KOKU app displays the number of completed training sessions and the remaining sessions required to complete the 12-week intervention. In addition to the structured training plan, participants may select additional exercises at any time from the pool of the 26 exercises. If KOKU is not used for two days, the app automatically generates a push notification reminder on the participant’s tablet device.

KOKU has recently been shown to be effective in improving functional outcomes, such as balance and lower-limb strength, in older adults [43]. A German-language version of KOKU has been evaluated in the SMART-AGE [44], where it showed excellent user experience, with no serious adverse events related to its use among community-dwelling older adults [45].

#### Personal coaching

The PC intervention for PA promotion will comprise three tablet-based video call sessions, each lasting about 45–60 min and conducted by trained physiotherapists or sports scientists. The PC is grounded in the principles of self-determination theory (SDT) [46], and integrates evidence-based BCTs [47]. The applied BCTs aims to promote the individual’s autonomy, sense of competence, and relatedness, which represent basic psychological needs according to SDT, thereby enabling participants to integrate PA in their daily routines. Key BCTs will include: (1) provision of information on the benefits of PA, (2) activity-related goal setting, (3) self-monitoring of PA, (4) feedback on PA behavior and related outcomes, (5) action planning, (6) use of prompts and cues for PA, (7) identification and management of PA-related barriers, (8) planning social support for PA, and (9) motivational interviewing (MI). BCTs 1–8, which aim to modulate personal beliefs and PA behavior, are embedded within the communication framework of motivational interviewing [48]. In accordance with this approach, participants and coaches interact on equal terms, reflected in a collaborative and informative communication style.

The PC sessions will be conceptually interconnected, with the BCTs implemented hierarchically across the three video calls. The first session will be conducted two weeks after initiation of KOKU, following the home visit. Based on participants’ previous and current experiences with PA during rehabilitation, they will be encouraged to set individually relevant activity-related goals and to develop action plans to implement these goals. Participants will be offered the option to self-monitor their PA and progress using a simple wrist-worn activity tracker (AS80, Beurer GmbH, Ulm, Deutschland), which they will receive during the home visit along with an introduction it its use and the associated app pre-installed on the tablet. This will allow participants to receive immediate feedback on their PA behavior.

Supplementary file 2 provides a detailed description of both interventions using the Template for Intervention Description and Replication (TIDieR) checklist [49].

### Control

Participants allocated to the CG will receive usual care, consisting of standard health and aged care services routinely available to older adults in the German healthcare systems. In addition, during the home visit, participants will be also provided with a tablet (with an introduction to its use) but without access to the KOKU app and without any PC sessions during the subsequent intervention period.

### Outcomes

An overview of primary, secondary, safety outcomes and descriptive measures are provided in Table 2. Data on all outcomes will be collected at the predefined time points according to the schedule of assessments. Except for DMOs, which will be recorded in participants´ home environments using wearable sensor technology, all measurements will be performed at the study center. To ensure optimal methodological rigor and standardization across assessments, all study personnel receive comprehensive training in all screening and assessment procedures prior to the initiation of participant recruitment.

**Table 2 Tab2:** Overview of primary, secondary, safety outcome and descriptive measures

Variables		T1 (1 week pre-OP)	T2 (6 weeks post-OP)	INT	T3 (6 months post-OP)
Sociodemographics					
DV	Age, sex, education, marital status, living situation, retirement status	X			
Clinical variables					
DV	Functional Comorbidity Index	X			
DV	Body Mass Index	X			X
DV	Charnley Classification	X			
DV	Fall history	X			
DV	Pre-operative hip characteristics (primary diagnosis, operated side, prior operations)	X			
DV	Surgical information (surgical technique, implant specification)		X		
DV	Range of hip motion, leg length discrepancy, gluteal insufficiency	X	X		X
Mobility					
*Real-world digital mobility outcomes* (AX6, Axivity Ltd., Newcastle, UK)					
PO	Step count	X	X		X
PO	Walking distance	X	X		X
SO	Walking duration, WB count, WB duration, walking speed, stride length, stride duration, cadence, walking variability	X	X		X
*Self-reported daily-life mobility*					
SO	Life-Space Assessment	X			X
SO	UCLA Activity Score	X			X
Physical capacity					
SO	6-Minute Walk Test^a^	X	X		X
SO	Timed Up and Go^a^	X	X		X
SO	30-Second Chair Stand Test	X	X		X
SO	4-Meter Gait Speed Test	X	X		X
SO	Global rating of change in self-perceived walking ability		X		X
Pain & hip function					
SO	Oxford Hip Score	X	X		X
DV	Oswestry Disability Index	X	X		X
Psychological factors					
SO	Short Falls Efficacy Scale-International	X	X		X
SO	Conscientiousness dimension – Big Five Inventory-2	X	X		X
SO	Behavioral Regulation in Exercise Questionnaire	X	X		X
DV	Short Scale of Technology Commitment	X			
DV	Patient Health Questionnaire-2	X			X
Executive functioning					
SO	Trail-Making Test A & B	X	X		X
Health status					
SO	EuroQol 5-Dimension 5-Level	X	X		X
SO	EuroQol Visual Analogue Scale	X	X		X
Falls					
SO	Fall calendar		X	X	X
Training adherence					
OPO	Exercise Adherence Rating Scale				X
OPO	Usage data of the training app				X
Intervention acceptability					
OPO	Theoretical Framework of Acceptability Questionnaire				X
OPO	5-point Likert scale on global acceptability				X
Health-related resource use					
OPO	Questionnaire for Health-Related Resource Use in an Elderly Population	X			X
DV	Type of post-acute rehabilitation program		X		
DV	Participation in other aftercare programs		X		X
DV	Usage of another training app		X		X
Intervention delivery costs					
OPO	Personnel, material, and travel expenses			X	
Harms					
SA	Complications & adverse events		X	X	X

Abbreviations: *INT* Intervention, *pre-OP* Preoperatively, *post-OP* Postoperatively, *DV* Descriptive variable, *PO* Primary outcome, *SO* Secondary outcome, *OPO* Other predefined outcome, *SA* Safety outcomes, *WB* Walking bout, *UCLA* University of California, Los Angeles

^a^instrumented with the mTEST³ system [mHealth Technologies srl, Bologna, Italy] to measure spatiotemporal gait parameters (6-Minute Walk Test) and durations of sit-to-walk, walking, turning, and sitting segments (Timed Up and Go)

#### Primary outcomes

The first primary outcome is the mean daily step count, and the subordinated primary outcome is the mean daily walking distance. Both DMOs will be recorded with a small (23.0 × 32.5 × 8.9 mm) and lightweight (11 g), water-resistant 6-axis inertial measurement unit (IMU; AX6, Axivity Ltd., Newcastle upon Tyne, United Kingdom), fixed at the participant’s lower back (L5 vertebra) using self-adhesive fixing foil, over a maximum measurement period of 7 consecutive days subsequently to the on-site assessments. After the measurement period, participants will remove the IMU themselves and return it to the study center in a prepaid, pre-addressed envelope. The IMU will be configured with a tri-axial accelerometer (range ± 8 g, accuracy 1 mg) and a tri-axial gyroscope (range ± 2000 dps, resolution 70 mdps), with a sampling frequency of 100 Hz. Raw data from the IMU will be standardized according to a predefined data structure described elsewhere [50]. The Mobilise-D computational pipeline (available at https://github.com/mobilise-d/mobgap), which consists of validated algorithms to derive DMOs [51–53], will then be used to identify WBs [54] and extract number of steps, duration, walking speed, stride length, cadence, and stride duration for each of these WBs. Walking distance per WB will be calculated by multiplying two validated DMOs: average walking speed × WB duration [55]. Steps and walking distances at the WB level will then be aggregated to daily level and averaged across up to 7 valid measurement days to yield mean daily step count and mean daily walking distance. A valid measurement is defined as ≥ 3 valid measurement days; a valid measurement day is defined with ≥ 12 h/day of wear time during waking hours (7 am – 10 pm), without weekday/weekend restriction [56].

#### Secondary outcomes

Secondary DMOs will be derived from the IMU recordings using also the validated Mobilise-D computational pipeline, applying the same valid-measurement criteria as for the primary outcomes: walking duration; number of WBs (all, > 10 s, > 30 s, > 60 s); WB duration and 90th percentile (P90) in WB duration; walking speed and P90 walking speed in WBs > 10 s and > 30 s; stride length (WBs 10–30 s and > 30 s); stride duration (all WBs and > 30 s); cadence (all WBs and > 30 s) and P90 cadence (WBs > 30 s); and bout-to-bout variability for WB duration (all WBs), walking speed and stride length (WBs > 30 s), cadence and stride duration (all WBs). Detailed definitions and the daily and weekly calculation procedures of these DMOs are provided elsewhere [34].

Self-reported daily-life mobility will be assessed using the Life-Space Assessment [57, 58] and the UCLA Activity Score [59].

Physical capacity will be measured using the 6-Minute Walk Test (6MWT) [60], the Timed Up and Go (TUG) [61], the 30-Second Chair Stand Test, and the 4-Meter Gait Speed Test [62]. The 6MWT and TUG will be instrumented with the mTEST3 system (mHealth Technologies srl, Bologna, Italy), a CE-certified sensor-based motion analysis system, to measure spatiotemporal gait parameters during the 6MWT (e.g., asymmetry, step length) and segments of movements during the TUG (e.g., sit-to-stand, walking, turning, stand-to-sit). Changes in self-perceived walking ability will be assessed with a 7-item Global Rating of Change scale [63].

Hip pain and function will be assessed using the Oxford Hip Score [64]. Back pain will be measured using the Oswestry Disability Index [65, 66].

Psychological factors will be evaluated using the Short Falls Efficacy Scale-International [67], the conscientiousness dimension of the Big Five Inventory-2 [68], and the Behavioral Regulation in Exercise Questionnaire (motivation regulation in PA) [69, 70].

Self-reported health status will be assessed using the EuroQol 5-Dimension 5-Level and the EuroQol Visual Analogue Scale [71].

Falls will be prospectively self-monitored by participants for each week after T2 assessment using fall calendars, which include documentation sheets to record the date, time, and location of the fall, the activity preceding the fall, and any fall-related injuries.

#### Other predefined outcomes

Adherence to the digital home-based exercise program will be assessed using the Exercise Adherence Rating scale [72] and usage data of the KOKU app.

Intervention acceptability will be evaluated using the Theoretical Framework of Acceptability questionnaire [73] and two separate 5-point Likert Scales on the global acceptability of the KOKU app and the PC intervention.

Health-related resource use will be assessed with an adapted version of the Questionnaire for Health-Related Resource Use in an Elderly Population (German: *‘Fragebogen zur Inanspruchnahme medizinischer und nicht-medizinischer Versorgungsleistungen im Alter’*), by use of the healthcare provider perspective, covering direct medical costs of formal healthcare services (e.g., physician visits, therapeutic services, rehabilitation, outpatient procedures, and hospital stays) within the past three months. Resource utilization will be converted into monetary values using standardized national unit costs [74].

Intervention delivery costs will include personnel, material, and travel expenses directly related to the interventions. Personnel costs will be derived from the national average wages of the professional groups involved, based on the time required for intervention implementation.

#### Descriptive variables

Age, sex, education, marital status, living situation, and retirement status will be collected as sociodemographic characteristics.

Clinical information will include comorbidities [75], body mass index, Charnley classification, fall history, preoperative hip characteristics (primary diagnosis, operated side, prior operations), surgical details (technique, implant specification), and hip function measures (range of hip motion, leg length discrepancy, gluteal insufficiency).

Technology acceptance (Short Scale of Technology Commitment; [76]) and depressive symptoms (Patient Health Questionnaire-2; [77, 78]) will be assessed as descriptive psychological factors. Descriptive variables for health-related resource use will include type of post-acute rehabilitation (outpatient, inpatient, or none), participation in other aftercare programs, and use of other training apps.

### Harms and safety monitoring

Postoperative complications occurring between the preoperative baseline assessment (T1) and the 6-week postoperative assessment (T2) will be recorded at the on-site T2 visit.

Adverse events (AEs) will be documented for the period from the 6-week postoperative assessment (T2) to the 6-month assessment (T3), regardless of any causal relationship to the interventions.

These will be recorded by telephone interview conducted by the coaches at the end of the intervention period and at the very end of the on-site 6-month assessment (T3) by assessors. In addition to systematically collected postoperative and AEs at scheduled assessments, interim events spontaneously reported by participants (e.g., via telephone calls) will also be documented as reported.

The severity of complications and AEs will be classified into: (1) mild = transient and easily tolerated events, causing no or minimal interference with activities of daily living (ADLs) and not requiring medical intervention; (2) moderate = events causing noticeable interference with ADLs and/or requiring minimal or noninvasive medical intervention; (3) severe = events resulting in marked limitation of ADLs, requiring medical intervention or hospitalization, including life-threatening events and death.

An independent Data Safety Monitoring Board (DSMB) will oversee participant safety and trial conduct. The DSMB will consist of an orthopedic surgeon, a geriatrician, and a biometrician. It will regularly review accumulating reports of AEs, assess their causal relationship with the interventions and severity classification, and make recommendations on potential modifications or discontinuation of the study. The DSMB will operate under a written charter specifying its roles, responsibilities, and decision-making processes.

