### Randomization and blinding

After the 6-week postoperative assessment (T2), participants will be randomized to one of three study arms in a 1:1:1 allocation ratio using permuted block sizes, stratified by type of post-acute rehabilitation (outpatient, inpatient, or none). The random allocation sequence will be generated automatically using the web-based tool randomizer.at (Institute for Medical Informatics, Statistics and Documentation, Medical University of Graz, Austria; https://www.randomizer.at). Allocation concealment will be ensured through this centralized, Good Clinical Practice-compliant web-based tool. Randomization will be performed exclusively by authorized study personnel with individual access credentials.

All primary and secondary outcome assessments will be undertaken by assessors blinded to group allocation. Other prespecified outcomes, including training adherence and intervention acceptability, will be collected using self-completed questionnaires provided to participants after the final 6-month postoperative assessment (T3). These will be completed at home and returned to the study center by mail using prepaid envelopes.

Usage data of the KOKU app will be downloaded from the tablets of participant in the IGs by assessors only after completing of the on-site T3 assessment.

AEs will be documented by the unblinded coaches during the intervention period (for participants of both IGs) and at the end of the intervention period (for all participants). At T3, AEs will also be recorded by blinded assessors, but only at the end of the visit, after all other on-site assessments have been completed.

Processing of the DMOs after return of the IMU will be conducted at T3 by blinded study personnel who are not involved in the on-site T3 assessment.

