### Statistical analysis

For the first primary endpoint, the null hypothesis states that there is no difference in the mean daily step count at 6-months post-THA (T3) between IG1 and CG. The primary analysis will use linear regression at a two-sided significance level of 5%, adjusting for the stratification factor post-acute rehabilitation (outpatient, inpatient, or none) and preoperative mean daily step count. If this hypothesis is rejected, the subordinated primary endpoint (mean daily walking distance) at T3 between IG1 and CG will be tested (adjusted for post-acute rehabilitation and preoperative mean daily walking distance).

Subsequently, the following hypotheses will be tested hierarchically: IG2 (KOKU alone) vs. CG for mean daily step count at T3; IG2 vs. CG for mean daily walking distance at T3; IG1 vs. IG2 for mean daily step count at T3; and IG1 vs. IG2 for mean daily walking distance at T3. If any test in this sequence cannot be rejected, all subsequent tests will be considered exploratory only. This hierarchy reflects the assumption that IG1 (KOKU with PC) is at least as effective as, or superior to, IG2 (KOKU alone).

The primary analysis follows the intention-to-treat principle, with participants analyzed according to their randomized group. Intercurrent events are handled as follows: for non-compliance, additional interventions, AEs after randomization, new illnesses, or falls occurring between T2 and T3, a treatment-policy strategy (ICH E9 (R1)) will be applied, such that the estimated treatment effect includes the impact of these events. Death unrelated to the intervention will be handled under a hypothetical strategy, assuming the intervention does not affect the timing or occurrence of death within the observation window. If the T3 assessment cannot be performed due to a training-related injury or fatal event clearly attributable to the intervention, a “worst outcome” (step count = 0 steps/day, walking distance = 0 m/day) will be imputed as a composite strategy.

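### The last scheduled adverse-event enquiry precedes the sensor week that yields both primary endpoints, so events in that week are not systematically collected (minor)

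*Protocol article*

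**What the plan says.** All references are to the protocol article.

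- **Harms and safety monitoring** sets the window: "Adverse events (AEs) will be documented for the period from the 6-week postoperative assessment (T2) to the 6-month assessment (T3". Enquiries are made by telephone at the end of the intervention period and "at the very end of the on-site 6-month assessment (T3) by assessors". In addition, "interim events spontaneously reported by participants (e.g., via telephone calls) will also be documented as reported".
- **Randomization and blinding** repeats the timing: "At T3, AEs will also be recorded by blinded assessors, but only at the end of the visit".
- **Primary outcomes** has the sensor worn "over a maximum measurement period of 7 consecutive days subsequently to the on-site assessments". Afterwards "participants will remove the IMU themselves and return it to the study center in a prepaid, pre-addressed envelope". A measurement needs at least 3 valid days, each with at least 12 h of waking wear time.
- **Statistical analysis** lists several intercurrent events and ends the list with "or falls occurring between T2 and T3, a treatment-policy strategy (ICH E9 (R1)) will be applied". It sets the outcome to 0 when the T3 assessment cannot be done because of a training-related injury or a death clearly attributable to the intervention. Values missing through dropout or loss to follow-up are multiply imputed under missing at random (MAR), with relevant intercurrent events in the imputation model.
- **Secondary outcomes** describes a weekly fall calendar starting after T2, with no end date; Table 2 marks it at T2, during the intervention and at T3.
- **Randomization and blinding** also shows that paper already travels by post after T3. Of the adherence and acceptability questionnaires it says: "These will be completed at home and returned to the study center by mail using prepaid envelopes".

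**The concern.** The order of events at T3 is visit, then adverse-event enquiry, then recording. Every day that contributes to the T3 step count and walking distance comes after the last planned opportunity to ask about falls, illness, injury or a skin reaction to the adhesive. Information not collected at that point cannot be recovered at analysis.

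Two things are at stake. The first is completeness of safety reporting for that week, during which participants wear a device and those in the intervention groups may still be using the exercise app, since continued use is allowed without limit. The second is attribution. The plan lets the cause of a missing T3 value decide which value is used: 0 for a training-related injury, a MAR imputation for dropout or loss to follow-up. If something in the recording week leaves too few valid days, no scheduled source says what it was.

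**Working it through.** The plan gives no figure for this gap, so the check rests on the stated visit windows and on following an event through the analysis rules.

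**1. Length of the gap.** Inputs from Study design and setting: T2 at 6 + 2 weeks, so weeks 6 to 8; T3 at 26 ± 2 weeks, so weeks 24 to 28.
- T2 to T3: shortest 24 − 8 = 16 weeks, nominal 26 − 6 = 20, longest 28 − 6 = 22.
- Recording week as a share of the time from T2 to the end of recording, 1/(w + 1): 1/17 = 5.9%, 1/21 = 4.8%, 1/23 = 4.3%.

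**2. Distance from the programme.** The intervention starts at 8 ± 2 weeks and lasts 12 weeks, so it ends at weeks 18 to 22 (nominal 20). The T3 visit follows by 24 − 22 = 2 to 28 − 18 = 10 weeks, nominal 26 − 20 = 6.

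**3. Two readings of T3.**
- If T3 is the visit, the recording week lies outside both the adverse-event window and the intercurrent-event window.
- If T3 includes the recording, both windows extend past the last enquiry meant to fill them. Randomization and blinding allows this reading, because it places sensor processing after device return at T3.

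On either reading the week has no scheduled enquiry.

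**4. What an event in that week does to the endpoint.**
- *At least 3 valid days remain.* The measured steps are analysed. For falls, illness and adverse events the treatment-policy strategy intends the effect of the event to be included, so the value is correct without an event record.
- *Fewer than 3 valid days remain* (5 or more of 7 days lost: 7 − 5 = 2 < 3). The endpoint is missing and its cause now matters: 0 if a training-related injury, MAR imputation otherwise. The text also does not say whether the rule imputing 0 applies when the visit took place but the recording failed.

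**5. Scale of one misattribution.** Assumption: the MAR-imputed value would lie between 5,000 steps (the plan's preoperative mean) and 6,500 (that mean plus the planned 1,500). With 71 participants per arm, classing one participant as 0 instead shifts the arm mean by:
- 5,000/71 = 70 steps, and 70/1,500 = 4.7% of the planned effect;
- 6,500/71 = 92 steps, and 92/1,500 = 6.1% of the planned effect.

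The documents give no frequency for such cases, so this is a shift per case and not an expected bias.

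**6. Whether it can still be changed.** Recruitment began in September 2025 and the article was submitted on 7 January 2026. From 1 September that is at most 128 days, about 18 weeks. The earliest T3 is 24 weeks after surgery, so no participant could have reached it by submission.

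**The case against.** The strongest case against is that the plan already has routes for these events and that the estimand barely needs them. Much of this stands.

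- A reader might infer that events in the recording week are never captured. The text does not support that. Spontaneous reports are documented, and the fall calendar runs weekly after T2 with no stated end. Both routes are partial: the reports are described as interim and are unsystematic, and the calendar covers falls only.
- A reader might infer that a fall or illness that week corrupts the primary step count, or that low activity cannot be told from non-wear. Neither follows. Treatment policy takes the steps as measured, and the 12 h wear criterion separates non-wear from inactivity.
- A reader might want to add the T1 wear week to the gap. That week is before surgery and randomization, so it cannot affect a between-arm comparison, and safety is summarised from randomization onward.
- The gap is the same length in every arm and falls nominally 6 weeks after the programme ends, so a training-related injury in that week is a residual case that depends on optional continued app use.
- The full protocol or analysis plan, not shown, may define when T3 ends and how reasons for failed recordings are logged. That could settle the definition. It would not remove the order of enquiry and recording that the article itself states.

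**Conclusion.** The point holds in limited form and is minor. As written, the last scheduled adverse-event enquiry comes before the whole of the primary-outcome recording, and no later safety contact is described. The uncovered period is at most 7 days, about 5% of post-T2 follow-up.

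The consequences are incomplete safety reporting for that week and an unsupported choice between two imputation rules when an event leaves fewer than 3 valid days. The primary analysis is not invalidated, and nothing in the documents suggests that more than isolated participants would be affected.

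The conclusion rests on the article's wording and assumes that the full protocol adds no contact after the sensor is returned.

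**What to change.** 1. Define the adverse-event and intercurrent-event window as running from T2 to the end of the T3 sensor recording, and state that the fall calendar runs to the same point.
2. Put a one-page sheet in the prepaid T3 sensor envelope for all arms, asking about fall, illness, injury, skin reaction, date, and reason for any early sensor removal. Enter the replies in the adverse-event log and the intercurrent-event data.
3. State whether the rule imputing 0 covers a completed T3 visit followed by a failed recording.

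The cost is a few sentences and one printed page in an envelope that is already mailed back. Some sheets will come back blank, so coverage of the week will improve without becoming complete.
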